## Abstract

Mental fatigue, induced by prolonged cognitive demands, impairs attention, decision-making, and motor coordination, potentially compromising performance in cognitively demanding sports such as football. This study presents a randomised controlled experimental design pre-test/post-test protocol designed to investigate the effects of mental fatigue on neurophysiological, visual, technical, and motor performance in football players. Thirty-four athletes (17 men, 17 women; aged ≥18 years; ≥1-year competitive experience) will be randomly assigned to either a cognitive fatigue induction group (30 min Stroop Task) or a low cognitive load control group. Data collection will include EEG (theta and alpha bands), eye tracking (fixation, saccades, pupil dynamics), sport-specific tasks (Loughborough Soccer Passing Test, Y-Shaped Agility Reaction Test), and subjective fatigue ratings (Fatigue Assessment Scale; Visual Analogue Scale). Statistical analyses will encompass intra- and inter-group comparisons, correlation and regression models. By integrating subjective, physiological, and performance indicators in a sport-specific, ecologically valid design, this protocol aims to deepen understanding of how mental fatigue affects performance and to inform individualized monitoring and intervention strategies in high-performance contexts. As a protocol paper, no data are yet available. However, based on previous literature, mental fatigue is expected to be associated with changes in EEG oscillatory activity, less efficient gaze behaviour, and impaired football-specific performance compared to the control condition.

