### Sample

2.2

Sample size was calculated using G*Power 3.1.9.7 software (41), considering a repeated measures ANOVA design with two groups (experimental *vs.* control) factors, and two measurement times (pre *vs.* post). The estimated minimum sample size at alpha 0.05 and statistical power of 80%, for moderate effect size (f = 0.25), was approximately 34 subjects (17 per group). At baseline, participants will be pre-screened using an online questionnaire to determine eligibility.

The inclusion criteria were: (i) minimum age of 18; (ii) at least one year of competitive football experience; (iii) no eye problems that impair vision; (iv) no history of neurological injuries; (v) abstinence of caffeine, alcohol and intense physical activities in the previous 24 h before each experimental session; (vi) having slept for at least 7 h the night before. On the other hand, the exclusion criteria were: history of neurological injury; uncorrected vision problems; diagnosis of psychological disorders; use of psychoactive substances in the last 24 h before the experimental sessions; any form of nystagmus for electrophysiological contraindications for electrophysiological recording. The operationalization and description criteria are summarized in Table 1.

**Table 1 T1:** Sample operationalization and description criteria.

Topic	Description	Operationalization
Age	Minimum age of 18 years	Participants aged 18 years or older. There is no maximum age limit stipulated in the protocol.
Gender	Gender balance	Sample of 24 men and 24 women, in equal number for experimental and control groups.
Competitive experience	Minimum of 1 year of competitive experience	Football players with a minimum of 1 year of regular practice in competitive condition
Health condition	No conditions preventing the practice of sport	Individuals with a history of neurological injuries, uncorrected visual problems, diagnosed psychological disorders, use of psychoactive substances in the last 24 h, or any clinical limitation to physical exertion will be excluded. Pregnant women will also be excluded.
Legal and ethical criteria	Compliance with current regulations	The study complies with the GDPR and the provisions of Decree-Law No. 5/2007, ensuring that all participants meet the legal and ethical conditions for physical exercise.

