##### VAS

2.5.4.2

The VAS for mental fatigue, applied immediately before and after the cognitive induction task (ST), captures acute fluctuations in the subjective perception of fatigue. This 100 mm continuous scale, anchored between “no fatigue” and “extreme fatigue”, is sensitive to short-term changes induced by cognitive load and task duration (84). Within the experimental group, VAS ratings will be compared pre and post ST to quantify the immediate impact of the intervention on mental fatigue.

In addition, associations between subjective fatigue and other objective markers will be explored. Specifically, post-intervention VAS results will be correlated with EEG spectral characteristics (particularly alpha and theta power), oculomotor parameters (blink rate, pupil diameter, saccadic dynamics, and fixations), and motor performance measures (LSPT and Y-SART). This approach allows us to determine whether higher levels of self-reported fatigue align with neurophysiological and behavioral indicators of reduced performance, providing a multimodal framework for validating the perceptual dimension of fatigue.

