#### Individual variability

2.5.5

Interindividual variability in responses to mental fatigue will be analysed to identify personal and sporting factors that modulate the impact of cognitive overload on neural, visual, and motor performance. This analysis will help clarify how specific athlete profiles cope with mental fatigue and maintain performance efficiency under cognitive stress.

Demographic and contextual variables such as age, gender, field position, training experience, sleep habits, caffeine consumption, and injury history will be considered. These parameters will be used as exploratory covariates to examine their moderating effect on the changes observed in the EEG, ETS, LSPT, and Y-SART results. Recent literature indicates that such individual factors modulate susceptibility to fatigue and help explain the variability in cognitive and physical performance under mental load (10, 13, 85).

This analysis will enable the differentiation of profiles that are more or less sensitive to mental fatigue, helping to map individual patterns of cognitive and physiological response to prolonged cognitive activity. It is expected that athletes with higher levels of competitive experience and attention self-regulation will show smaller decreases in performance and smaller neurophysiological changes. This personalized approach, integrated with objective and subjective data, will contribute to the development of individualized strategies to optimize cognitive and neuromotor resilience in demanding sporting environments.

While individual characteristics will be considered as exploratory covariates, the present sample size and experimental structure are primarily oriented toward detecting overall fatigue-related effects rather than complex interaction models between multiple individual variables. Future studies specifically designed to recruit more homogeneous samples (e.g., athletes from the same competitive level or age group) may allow a more in-depth analysis of interindividual variability in mental fatigue responses.

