For EEG data (theta, alpha, and beta bands), spectral power within predefined regions of interest (ROIs) will be analyzed using repeated-measures models including Time (pre vs. post mental fatigue) and Recording Condition (eyes open, eyes closed, motor imagery), allowing evaluation of fatigue-related changes across neural states. Primary analyses will focus on frontal midline and posterior ROIs, consistent with the study's theoretical hypotheses. Exploratory analyses across additional scalp regions will be conducted separately and corrected using False Discovery Rate (FDR) procedures to control for multiple comparisons. Correlational analyses (Pearson's r) will explore associations between EEG bands and behavioral performance (LSPT, Y-SART), as well as subjective fatigue scores (VAS and FAS) (94, 95). Topographic maps will be generated to visualize EEG power distributions across cortical regions.

For oculomotor parameters (fixations, saccades, pupil diameter, blink rate), comparisons will assess the impact of mental fatigue on attention dynamics and visual search efficiency. Pearson correlations will explore links between ETS metrics, EEG patterns, and motor performance scores. Eye-tracking outcomes will be interpreted in conjunction with EEG measures, motor performance variables, and subjective fatigue scores, allowing a multimodal framework that reduces interpretative ambiguity.

Motor performance will be analyzed by comparing LSPT and Y-SART results before and after cognitive induction. Metrics such as execution time, technical penalties, and reaction times will be examined to determine whether cognitive fatigue impairs decision-making and technical execution under pressure.

These performance results will be correlated with neurophysiological and oculomotor indicators to investigate predictive relationships. Subjective fatigue will be analyzed using pre and post VAS comparisons and baseline FAS scores. These will be used to triangulate subjective perceptions with objective changes in EEG, ETS, and performance data. Higher self-reported fatigue scores are expected to align with reduced cortical efficiency, altered visual behavior, and degraded motor output.

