To address individual variability, demographic and contextual variables (e.g., age, gender, field position, experience, sleep habits, caffeine intake) will be tested as covariates using ANCOVA or subgroup analyses. This will help determine whether certain profiles exhibit greater resilience or vulnerability to mental fatigue (10, 96).

Finally, multimodal integration will involve constructing correlation matrices and regression models to identify fatigue profiles across domains. This will allow for the identification of converging patterns across the EEG, ETS, motor, and subjective domains, thereby increasing the understanding of the neurocognitive and behavioral effects of mental fatigue. This approach is supported by advanced multivariate methodologies in sports neuroscience and applied psychology (39, 40).

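### The exploratory cross-domain Pearson correlations name no adjustment for sex in a sample that is half men and half women by design

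*Protocol article*

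**What the plan says.** **Method.** Section 2.6 of the protocol article names Pearson's r for each set of cross-domain links. For EEG: "Correlational analyses (Pearson's r) will explore associations between EEG bands and behavioral performance (LSPT, Y-SART", with the VAS and FAS scores added in the same sentence. For eye tracking: "Pearson correlations will explore links between ETS metrics, EEG patterns, and motor performance scores". The Discussion again gives Pearson's correlation as the tool for links between domains. The section ends with a multimodal step: "multimodal integration will involve constructing correlation matrices and regression models to identify fatigue profiles across domains". Its intended reading follows: "This will allow for the identification of converging patterns across the EEG, ETS, motor, and subjective domains". No partial, sex-stratified or sex-adjusted correlation is described, and no regression predictors are listed.

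**Sex mix.** The Abstract has "Thirty-four athletes (17 men, 17 women; aged ≥18 years; ≥1-year competitive experience". Table 1 in section 2.2 has "Sample of 24 men and 24 women, in equal number for experimental and control groups". The totals disagree (34 against 48), but both are half men and half women.

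**Gender.** The article does plan to use gender, in four places:
- Section 2.2 says the questionnaire data, which include gender, will help deal with confounding. It names no analysis.
- Section 2.5.5 says of the demographic and contextual variables: "These parameters will be used as exploratory covariates to examine their moderating effect on the changes observed".
- Section 2.6 tests gender among other covariates by ANCOVA or subgroup analyses.
- The Discussion allows ANCOVA for individual variability where appropriate.

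**Levels or changes.** Section 2.5.4.2 uses a level: "post-intervention VAS results will be correlated with EEG spectral characteristics (particularly alpha and theta power", and likewise with oculomotor and motor measures. Section 2.5.1.2 sets band power values against LSPT and Y-SART results, which also reads as levels. For the other pairs the scale is not fixed.

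**The concern.** A correlation pooled over two groups has a within-group part and a part that comes from the difference in group means. If men and women differ on average in a motor time and also in an EEG or gaze level, the two measures correlate across players even when they are unrelated within each sex. For given differences, a half-and-half mix makes this second part as large as it can be.

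Randomisation does not protect against this, because these are associations between people and not arm contrasts. Adjusting for arm does not remove it either, since Table 1 intends sex to be balanced between arms.

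The article puts weight on these associations. Section 2.5.6 treats alignment between modalities as support for the validity of fatigue assessment and expects composite markers to emerge. A correlation produced by sex would be reported as convergence. Sex differences of the opposite sign could hide a real within-sex relation.

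**Working it through.** The article gives no figure on this point to reproduce. Its sample size of 34 (f = 0.25, 80% power, alpha 0.05) can be reproduced with an assumed pre-post correlation of 0.5, at which power is 0.807. That calculation concerns the repeated-measures ANOVA and has no bearing here.

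**Inputs from the article.** Half men and half women (Abstract, Table 1); N = 34, or 48 under Table 1; 5% significance level (section 2.6).

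**Assumptions.** Two-sided tests, normal measures, and no correlation within either sex. The sex differences d1 and d2, in within-sex SDs, are assumed because the article gives none; they are shown as a range.

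**Formula.** With proportion p of men, the sex means add p(1−p)·d1·d2 to the covariance and p(1−p)·d² to each variance. At p = 0.5, p(1−p) = 0.25, its maximum, so

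r = (d1·d2/4) / √[(1 + d1²/4)(1 + d2²/4)].

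- d1 = 1.2, d2 = 0.5: 0.15 / √(1.36 × 1.0625) = 0.15 / 1.202 = 0.125.
- d1 = 2.0, d2 = 1.0: 0.50 / √(2.00 × 1.25) = 0.50 / 1.581 = 0.316.
- d1 = 1.0, d2 = 0: r = 0. Both measures must differ by sex.

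**Rejection rates.** The critical |r| is 0.339 at N = 34 (32 df) and 0.285 at N = 48. Rates come from simulation with at least 40,000 trials per setting. The partial correlation given sex is tested on 31 df at N = 34.

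| d1, d2 | induced r | plain r, N = 34 | plain r, N = 48 | partial r, both N |
|---|---|---|---|---|
| 1.0, 0 | 0 | 5% | 5% | 5% |
| 0.5, 0.5 | 0.06 | 6% | 7% | 5% |
| 1.2, 0.3 | 0.08 | 7% | 8% | 5% |
| 2.0, 0.3 | 0.10 | 9% | 11% | 5% |
| 1.2, 0.5 | 0.125 | 11% | 13–14% | 5% |
| 1.0, 1.0 | 0.20 | 21% | 28% | 5% |
| 2.0, 1.0 | 0.316 | 47% | 63% | 5% |

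A larger sample makes the false-positive rate worse, because the induced r does not shrink with N.

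**Masking.** With a within-sex correlation w, the numerator becomes w + d1·d2/4. At d1 = d2 = 1.0, a true w of −0.25 gives a pooled correlation of exactly zero.

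**Changes.** A sex difference that is the same before and after cancels when post minus pre is taken. The artefact then remains only if men and women differ in their response in both measures.

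**The case against.** The strongest reply is that this is an exploratory analysis in an article that does not ignore gender. It collects gender, says confounding will be dealt with, and plans ANCOVA and subgroup analyses. All of that is true, so the gap is narrow: none of these provisions is attached to the correlations. The provisions in sections 2.5.5 and 2.6 concern how outcomes vary with player characteristics, not how two outcomes relate to each other.

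A reader might infer that the multimodal regressions are to be run without a sex term. The article does not say so. It lists no predictors, so sex is neither included nor excluded, and a journal article may leave that list to the full plan.

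A reader might also take the high rejection rates as what this trial will see. The article does not support that. It gives no sex difference for LSPT, Y-SART, EEG, pupil or blink measures. The 47% belongs to the extreme of the assumed range, and the rate is close to nominal when the difference is small in either measure.

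It is also fair to say that the scale is open for most pairs and that section 2.6 speaks of objective changes when it describes triangulation. If changes are correlated, the table largely does not apply. The post-intervention VAS and band-power correlations, however, are described as levels. Nor does the article state outright that the correlations pool all players. If they were confined to one arm, the induced r would be the same for the same half-and-half mix, but the tabulated rates would not apply.

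Finally, sex is one of several listed covariates. It merits separate treatment because its share is fixed by design at the value where the artefact is largest.

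**Conclusion.** The point holds in a limited form. Plain Pearson r is the named method, the sample is half men and half women by design, at least some pairs use levels, and the planned gender analyses do not reach these correlations. A correlation that reflects only sex could therefore be read as convergence between fatigue markers, or a real one could be hidden.

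The size is conditional on sex differences that the article does not supply. It ranges from no inflation when only one measure differs to about 47% false positives at N = 34 when the differences are 2.0 and 1.0 SD. It also rests on levels being correlated and on no within-sex relation. No group comparison and no primary EEG contrast is affected. The change is worth making because a better method is available from data already collected, not because the harm is established.

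**What to change.** In section 2.6:
- State that cross-domain correlations on levels are computed as partial correlations given sex.
- State for each pair whether levels or pre-post changes are correlated.
- State that sex is a term in the multimodal regressions, and list their predictors.

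Marking men and women with different symbols in scatter plots is optional presentation.

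The cost is one degree of freedom per correlation (31 instead of 32 at N = 34), which raises the critical |r| from 0.339 to 0.344. Gender is already collected by questionnaire, so no new data are needed.

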The absence of integrated protocols limits not only the ecological validity of results, but also their applicability to training and performance contexts. Recently, the importance of more comprehensive and ecologically valid experimental designs—simultaneously integrating assessments of athletes' physical, technical, and cognitive performance –, has been advocated in the literature (7, 27); primarily because mental fatigue diminishes not only physical and technical skills, but also interferes with the attentional resources necessary for efficient execution of football-specific tasks (2, 6, 12).

This study proposes a methodology and an experimental protocol to assess mental fatigue and its effects on physical performance in football. Subjective and objective instruments will be used to assess mental fatigue, namely: FAS, to measure the general level of physical and mental fatigue; VAS, applied at different times to capture moment variations in fatigue perception; ETS, to analyze saccades, blink rate, pupil dilation, and fixation pattern as markers of cognitive overload; and EEG, recording the brains electrical activity, with a focus on frontal theta and alpha bands associated with attention and executive control. Physical performance will also be assessed via two motor performance tests: LSPT, which assesses technical accuracy and decision-making under time pressure; and Y-SART, measuring the agility and reaction time to visual stimuli (38).

There is a clear need for an ecologically-valid, football-specific experimental protocols integrating neurophysiological, visual, subjective and sport-specific motor measures within a single, coherent design. The present protocol describes a randomised controlled pre-post protocol design to examine how acute mental fatigue affects cortical activity, gaze behaviour and technical-motor performance in football players.

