### Performance assessment

2.4

After collecting baseline data, participants will perform two motor tests as part of Phase 3 of the protocol. The first is the LSPT, which assesses passing accuracy and speed under time pressure in a standardized soccer-specific context. Participants perform 16 passes to designated targets announced in sequence, with performance assessed by total execution time adjusted for penalty points for technical errors (e.g., incorrect passes, errors in the target area, poor ball handling) and bonus points for accurate actions. This scoring protocol has been validated in youth and elite football players (56, 57). The test will be filmed with two cameras for subsequent technical analysis and penalty verification. A schematic representation of the LSPT setup is provided in Figure 2, adapted from Ali et al. (34).

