**Figure 2 F2:**
[figure not shown]
Schematic representation of the LSPT, adapted from Ali et al. (34).

The second physical performance test is the Y-SART, designed to assess agility and reaction time to visual stimuli. Participants start the course from a fixed point and, after an initial start, must react to a visual stimulus provided by the WITTY SEM system, which indicates the need to deviate to the left or right on the Y-SART course. Times are automatically recorded from the start to the finish line, ensuring accurate measurement of reaction and movement speed. A schematic representation of the Y-SART configuration is also provided, in Figure 3, adapted from Yuan et al. (2).

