##### LSPT

2.5.3.1

In the LSPT, the variables total execution time, technical penalties, and adjusted score will be analysed, indicators that simultaneously integrate motor speed, technical accuracy, and cognitive efficiency under time pressure. This protocol demonstrates high ecological validity and excellent test-retest reliability for assessing technical proficiency and decision-making performance in football (4, 57). Recent evidence shows that mental fatigue leads to an increase in total time and penalty time, indicating that mentally fatigued athletes are more prone to technical errors, such as missing target zones. This decline in performance appears to stem from a shift in attention towards irrelevant stimuli rather than task-relevant stimuli, resulting in poorer technical execution and slower motor fluency (80, 81).

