##### Y-SART

2.5.3.2

The Y-SART will use the Witty SEM system to deliver random light stimuli requiring rapid directional responses. Reaction and execution times will be recorded as indicators of visuomotor coordination and decision-making efficiency under cognitive load. Under conditions of mental fatigue, an increase in reaction time is expected in the Y-SART, reflecting slower perceptual-decision processing and reduced cognitive readiness, while execution time may also show moderate increases due to delayed motor initiation. This pattern is consistent with the evidence that reactive agility performance is particularly sensitive to cognitive overload and fatigue effects (82).

In line with Khalaji et al. (14), who reported impairments in decision-making accuracy and execution speed following mental fatigue induction, the present study employs the LSPT and Y-SART to assess the behavioral impact of cognitive overload in football contexts.

Although the protocol is conducted in a controlled laboratory setting, the selected football-specific tests require multidirectional actions and quick responses to external cues, partially reflecting perceptual and decision-making demands present in match play. The controlled environment helps reduce external influences while maintaining key sport-specific elements.

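### The motor tests are to show whether fatigue impairs decision-making, but no listed motor outcome measures decision accuracy and at most one of the five measures decision speed

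*Protocol article*

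**What the plan says.** **The inference.** Section 2.6 states the purpose of the motor analysis: "Metrics such as execution time, technical penalties, and reaction times will be examined to determine whether cognitive fatigue impairs decision-making and technical execution". The Discussion adds that, if the hypothesis is confirmed, decision performance as well as motor performance will be shown to suffer.

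**The LSPT.** The Introduction describes the "LSPT, which assesses technical accuracy and decision-making under time pressure", and section 2.5.3.1 also credits the test with assessing decision-making. The procedure in section 2.4 reads: "Participants perform 16 passes to designated targets announced in sequence". Performance there is "total execution time adjusted for penalty points for technical errors (e.g., incorrect passes, errors in the target area, poor ball handling"), with bonus points for accurate actions. Section 2.5.3.1 names what is analysed: "In the LSPT, the variables total execution time, technical penalties, and adjusted score will be analysed".

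**The Y-SART.** In section 2.4 the player reacts to a light that signals left or right, and section 2.5.3.2 says the stimuli are random. On timing, section 2.4 says: "Times are automatically recorded from the start to the finish line". Sections 2.5.3 and 2.5.3.2 list reaction time and execution time, and the latter section reads them as indicators of how efficiently decisions are made. Section 2.3, explaining why eye tracking is not used in this test, says that motor skills are its main determinant and that perceptual processes contribute less, or only indirectly.

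**The precedent.** Section 2.5.3.2 aligns both tests with a study "who reported impairments in decision-making accuracy and execution speed following mental fatigue induction".

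**The concern.** The plan names a conclusion about decisions, but it lists outcomes that mostly cannot tell a decision from the movement that carries it out.

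For the LSPT, a slower or more heavily penalised run after the Stroop task could come entirely from poorer ball control or slower running and still be reported as impaired decision-making. For the Y-SART, a player who commits earlier and turns the wrong way more often could show unchanged times and look unimpaired. Without a count of wrong turns, that trade of accuracy for speed would not be seen.

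The article's Conclusion offers the results to coaches partly as a basis for protecting athletes' decision-making capacity, so the distinction matters to those who would use the findings.

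**Working it through.** The plan gives no figure on this point to reproduce. The sample size of 34 plays no part in it. The check sets each listed outcome against what it can show.

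**Step 1. List the motor outcomes** (sections 2.5.3, 2.5.3.1 and 2.5.3.2). There are three for the LSPT and two for the Y-SART: 3 + 2 = 5.

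| Listed outcome | Decision accuracy | Decision speed |
|---|---|---|
| LSPT total time | No | Not separable from ball control and movement |
| LSPT technical penalties | No, error types grouped | No |
| LSPT adjusted score | No, combines time, penalties and bonuses | Not separable |
| Y-SART reaction time | No | Yes, if timed from stimulus onset |
| Y-SART execution time | No | Not separable from running |

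Decision accuracy: 0 of 5. Decision speed: at most 1 of 5.

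**Step 2. What an LSPT change identifies.** Write the penalties as P = P(incorrect pass) + P(target area) + P(ball handling) + any other types, and the adjusted score as S = T + P − B, with T the time and B the bonuses. This is notation only; the article gives no weights. A rise in P is compatible with no change at all in P(incorrect pass). A rise in S is compatible with no change in P. Only P(incorrect pass) could reflect a misidentified target, and it is not listed as a variable. Because the targets are announced, the player does not select them, so the remaining components are about execution and speed. Section 2.4 itself introduces the test as one of passing accuracy and speed, which fits its procedure better than the wider description in the Introduction.

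**Step 3. What a Y-SART change identifies.** Start-to-finish time = run before the stimulus + reaction + movement after it. Reaction time is a named outcome, but the only timing described is start to finish, and no separate point for the response is given. If the reaction component is not isolated, the recorded time is mostly movement, which agrees with the statement in section 2.3 that motor skills dominate. Section 2.5.3.2 nevertheless reads these times as evidence on decisions. The two sections describe the test differently according to the purpose at hand.

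**Step 4. Compare with the precedent.** The cited study is said to have reported both decision-making accuracy and execution speed. Execution speed has a counterpart among the five outcomes. Decision accuracy has none.

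**The case against.** A reader might infer that nothing in the trial measures a decision. The documents do not support that. Time to respond to an unpredictable left/right light is a choice reaction time, and the plan lists it separately from execution time. Section 2.5.3.2 expects it to lengthen through slower perceptual and decision processing, and an inference about speed needs no accuracy score. This part of the objection stands, and it is why the count for decision speed is at most one rather than none. It is also why the remedy must not bar a decision-speed claim.

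A reader might also infer that the LSPT is invalid as a measure of decision-making, or that the player has nothing at all to decide. That goes too far. The article cites validation work that is not available here, and the setup figure is not shown. What the text does establish is narrower: targets are announced, and the analysed variables do not separate kinds of error.

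Three further points deserve weight:

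- **Decision-making is not in the formal hypothesis.** The hypothesis at the end of the Introduction speaks of football-specific performance, and section 2.5.3.2 says the tests reflect decision demands only in part. This limits the reach of the concern, but section 2.6 still states the inference outright.
- **The lists are open.** Section 2.6 introduces its metrics as examples, the error types are also examples, and a condensed article may leave scoring detail to a fuller protocol. The article does not say that error types will stay merged. However, the analysed variables and the conclusion to be drawn are both stated, and they do not match. That mismatch is not a matter of missing detail.
- **The precedent is one sentence.** The main justification for the tests lies elsewhere, so the comparison in step 4 is supporting evidence only.

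**Conclusion.** The concern holds in a limited form. The five listed motor outcomes include no measure of decision accuracy and at most one of decision speed. LSPT time, penalties and adjusted score cannot separate impaired decisions from worse technique or slower movement, so they should not be used to conclude that decision-making is impaired. Y-SART reaction time can support a conclusion about the speed of a simple two-option decision, provided it is timed from the stimulus and kept apart from movement.

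This rests on three readings: that the task descriptions in section 2.4 are complete enough to show who selects the target, that an incorrect pass includes a pass to the wrong target, and that the variables named in sections 2.5.3 to 2.5.3.2 are those to be analysed. The trial's conclusions on technical execution, speed, EEG, gaze and perceived fatigue are unaffected. The change should be made, because one stated conclusion goes beyond its data and, by the Abstract, no data are yet available.

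**What to change.** In sections 2.5.3 and 2.6:

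1. Limit LSPT total time, penalties and adjusted score to conclusions about technical execution and speed, and align the descriptions of the test in the Introduction and section 2.5.3.1 with this.
2. Count wrong-target passes separately from execution penalties, using the two-camera LSPT video already planned for penalty verification.
3. Record wrong-direction Y-SART responses during testing and report them beside the times. The cameras are described only for the LSPT, so the tester would need to keep this tally.
4. State how Y-SART reaction time is obtained. Allow a decision-speed conclusion only from a reaction time measured from stimulus onset, separately from movement time.
5. Allow a decision-accuracy conclusion only from the two error counts. If they are too sparse to analyse, say that decision accuracy was not tested.

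The cost is revised wording, one extra tally per test and confirmation of the Y-SART timing. The downside is a narrower claim, and with about 34 players the error counts may be too few to analyse.
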